### Provisions for post-trial care {30}

Participants will be in the study for a duration of at least 24 months. Follow-up will continue for each participant after 24 months to the end of the trial (i.e. last patient, last visit), with follow-up after 24 months embedded in routine clinical care as per the respective country guidelines. At each post-trial visit, participants will be asked about TB symptoms and other safety outcomes.

### Outcomes {12}

#### Primary outcome

The primary outcome is the occurrence of probable or definite TB disease. Definite TB disease will be diagnosed by a culture or Xpert positive result for *M. tuberculosis.* Probable TB will be diagnosed according to an algorithm that takes into account symptoms, chest x-ray reading, sputum smear, histology and verbal autopsy results (see Table 1).

#### Secondary outcomes

Occurrence of possible, probable or definite TB disease. We will include those from the algorithm referred to above who are defined as possible TB.Occurrence of an adverse eventTreatment completion, defined as ≥ 11 of 12 doses of treatment over no more than 16 weeksAll-cause mortalityOccurrence of possible, probable or definite TB, or death, noting that a proportion of deaths are likely to be due to TB but not possible to confirm through verbal autopsy and clinical notes review.

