### Objectives {7}

The primary objective of this study is to assess the efficacy of preventive therapy with a 12-week course of rifapentine and isoniazid (3HP) against the development of probable or definite TB disease (see Table 1) over 24 months in people with DM who are LTBI test positive.

**Table 1 Tab1:** TB diagnostic criteria

Symptom and x-ray result	Investigation results	Definition
**Symptom positive and typical TB on x-ray**	Sputum culture or Xpert positive	Definite TB
	Sputum smear positive, culture negative/not available and Xpert negative/not available	Probable TB
	Sputum smear negative, culture negative/not available and Xpert negative/not available	Possible TB
**Symptom positive, possible TB on x-ray (including extra-pulmonary findings)**	Sputum culture or Xpert positive	Definite TB
	Sputum smear positive, culture negative/not available and Xpert negative/not available	Probable TB
	Sputum smear negative, culture negative/not available and Xpert negative/not available	Possible TB
	Histopathology positive, culture negative/not available and Xpert negative/not available	Probable TB
	Other sample culture or Xpert positive	Definite TB
**Symptom negative, typical TB on x-ray**	Sputum culture or Xpert positive	Definite TB
	Sputum smear positive, culture negative/not available and Xpert negative/not available	Probable TB
	Sputum smear negative, culture and/or Xpert negative	Possible TB
**Symptom positive, normal x-ray**	Sputum culture positive	Definite TB
	Sputum smear positive, culture negative/not available and Xpert negative/not available	Possible TB
	Sputum smear negative, culture negative/not available and Xpert negative/ not available	Not TB
	Histopathology positive, culture negative/not available and Xpert negative/ not available	Probable TB
	Other sample culture or Xpert positive	Definite TB
**Symptom negative, possible TB on x-ray (including extra-pulmonary findings)**	Sputum culture or Xpert positive	Definite TB
	Sputum smear positive, culture negative/not available and Xpert negative/not available	Possible TB
	Sputum smear negative, culture negative/not available and Xpert negative/not available	Possible TB
	Histopathology positive, culture negative/not available and Xpert negative/ not available	Probable TB
	Other sample culture or Xpert positive	Definite TB

^1^A positive GeneXpert is regarded as having the same status as a positive culture result

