#### Criteria for discontinuing or modifying allocated interventions {11b}

Trial participants may choose to discontinue the trial treatment at any time without penalty or loss of benefits to which they are otherwise entitled. Although the participant is not required to give a reason for discontinuing their trial treatment, a reasonable effort will be made to establish this reason while fully respecting the participant’s rights. Participants who discontinue treatment should remain in the trial for the purpose of follow-up and data analysis (unless the participant withdraws their consent for follow-up).

The following criteria may result in treatment interruption:
Occurrence of an adverse eventRequirement for prohibited medicationsPregnancy or breastfeeding (permanent discontinuation)Diagnosed with TB by a clinician, warranting anti-TB treatment (permanent discontinuation)Request by the participant to stop treatmentIntercurrent illness or change in the participant’s condition that justifies the discontinuation of treatment in the treating physician’s opinion and after discussion with the site PIInadequate compliance with the protocol treatment in the judgement of the treating physician

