### Sample size {14}

We expect to screen approximately 6000 individuals in order to recruit 3000 patients with DM and LTBI for the RCT. In an unpublished case-control study (excluding HIV patients) in Uganda, the prevalence of LTBI among the DM patients as well as controls was ~ 70% using Quantiferon only.

With an incidence rate of 22.5 TB cases/1000/year, we will have 90% power to detect a RR of 0.5 or less with 3000 individuals randomised (allowing for 10% loss to follow-up). Sensitivity analyses to assess the power of our study under a range of plausible parameter estimates are shown in Table 4. Incidence rates of TB were estimated from prevalence studies, assuming an average disease duration of 2 years. With respect to efficacy, no data are available in DM patients, but a Cochrane Review of 12 trials with 8578 HIV-infected participants reported TB preventive treatment (any anti-TB drug) had a lower incidence of active TB than placebo (RR 0.68, 95% CI 0.54–0.85) [32]. The benefit was greater in TST-positive individuals (RR 0.38, 95% CI 0.25–0.57) than TST-negative individuals (RR 0.89, 95% CI 0.64–1.24) [28]. Risk reduction is expected to be at least as great for DM, and to justify policy change, we envisage that at least 50% efficacy would be needed. TB incidence is expected to stay relatively constant in people with DM (as opposed to the decreasing incidence observed in TB case contacts) which means it is worthwhile to continue follow-up for all trial participants until the last randomised participant completes 24 months of follow-up, in order to maximise power.

**Table 4 Tab4:** The total number of people needed (with 1:1 randomisation) for detecting a given reduction in risk with 90% power and a significance level of 0.025 (one-sided)

	Cumulative number of cases/1000 over 2 years of follow-up		
RR	30/1000	40/1000	50/1000
0.4	2664	1982	1574
0.5	4106	3054	2424
0.6	6834	5082	4032

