### Assignment of interventions: allocation

#### Sequence generation {16a}

Participants will be randomised 1:1 to intervention or placebo using blocked randomisation within strata (clinical sites), with random block sizes. The randomisation list will be generated and managed by a validated module in the CASTOR database.

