### Statistical methods

A summary of the statistical approaches is provided here. Full details are outlined in the Statistical Analysis Plan. All efficacy comparisons test hypotheses of the superiority of RPT/INH against placebo, with a significance level of 0.025 (one-sided).

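### Possible TB in symptom-free, sputum-negative participants needs no change from the screening x-ray, so a stable baseline shadow can count as a secondary-endpoint event and pull those rate ratios towards 1

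*Protocol article*

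**What the plan says.** All references are to the protocol article.

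- **Secondary outcomes (Outcomes {12}).** The first secondary outcome is possible, probable or definite TB. Its possible cases come from the Table 1 algorithm: "We will include those from the algorithm referred to above who are defined as possible TB". The last secondary outcome combines the same endpoint with death.
- **Table 1 (Objectives {7}).** Cases are sorted by symptoms, x-ray category and test results. In the group headed "Symptom negative, possible TB on x-ray (including extra-pulmonary findings", a negative smear with culture and Xpert negative or not available gives Possible TB. In the symptom-negative group with a typical film, a negative smear with negative culture and/or Xpert also gives Possible TB. No row or footnote refers to an earlier film.
- **Table 1 footnotes.** Footnote 2 says that the definitions concern the initial evaluation. The only change of label it describes is from possible to probable after a clear treatment response. Footnote 3 describes an endpoint committee, but only for deaths without a recent TB evaluation.
- **Exclusion criteria.** There is no x-ray criterion. Previous TB disease excludes if it was confirmed, or diagnosed and treated. Current disease excludes if "Diagnosed with TB by a clinician, warranting anti-TB treatment" applies (the same words recur under {11b}).
- **Table 3 (Participant timeline {13}).** Chest x-ray is scheduled at screening, month 12 and month 24. Sputum is taken if indicated. At screening only Xpert is used for diagnosis.
- **Additional analyses {20b}.** Both TB-containing secondary outcomes are analysed in the same way as the primary: a site-adjusted Poisson rate ratio.

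**The concern.** An old, inactive shadow in someone never treated for TB and Xpert-negative at screening is compatible with randomisation. If the month 12 or month 24 film shows the same shadow and sputum is taken and is negative, the printed rule labels that person Possible TB, and the secondary outcome counts the label as an occurrence of TB.

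Such a finding precedes randomisation, so 3HP cannot prevent it, and randomisation balances it between arms in expectation. Adding roughly equal numbers of unpreventable events to both arms moves a ratio below 1 towards 1. The broader TB endpoint could then show much weaker efficacy than the primary endpoint, and readers could take the gap for a real loss of effect. Under Sample size {14} the protocol names 50% efficacy as what a policy change would need. That threshold is not tied to this endpoint, but readers are likely to compare the two.

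**Working it through.** **1. The plan's own figure.** Inputs from Sample size {14}: a control rate of 22.5 per 1000 per year, a 10% allowance for losses, and this power claim: "we will have 90% power to detect a RR of 0.5 or less with 3000 individuals randomised". The significance level is one-sided 0.025 (Statistical methods). Allocation: "Participants will be randomised 1:1 to intervention or placebo".

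Two-year control risk p0 = 2 × 0.0225 = 0.045; p1 = 0.5 × 0.045 = 0.0225; mean 0.03375.

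n per arm = [1.960 × √(2 × 0.03375 × 0.96625) + 1.282 × √(0.045 × 0.955 + 0.0225 × 0.9775)]² / 0.0225² = 1352.

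Total evaluable 2704, and 2704 / 0.9 = 3005, against 3000 in the protocol. The same formula gives all nine Table 4 cells exactly. The planning values are therefore a sound base: 3000 × 0.9 / 2 = 1350 evaluable per arm.

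**2. Adding counted shadows.** Let s be the share of participants, equal in both arms, whose stable shadow is actually labelled Possible TB. The document gives no value for s, so the range is an assumption.

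True events over 2 years: control 1350 × 0.045 = 60.75; intervention 30.375.

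RR(s) = (30.375 + 1350s) / (60.75 + 1350s)

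| s | added per arm | RR | apparent efficacy |
|---|---|---|---|
| 0 | 0 | 0.50 | 50% |
| 1% | 13.5 | 43.875 / 74.25 = 0.59 | 41% |
| 2% | 27 | 57.375 / 87.75 = 0.65 | 35% |
| 5% | 67.5 | 97.875 / 128.25 = 0.76 | 24% |

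If a person counted for a shadow can no longer contribute a true event, the risks are s + (1 − s) × 0.045 and s + (1 − s) × 0.0225. The RR is then 0.59, 0.66 and 0.77, almost the same. Under that version, power for a comparison of 1350 per arm falls from 0.90 to 0.81, 0.72 and 0.53. The trial was not sized on this endpoint, so these power figures only show scale.

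**3. What makes the dilution smaller (at s = 2%).**

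- *Genuine possible TB adds true events.* The 45/1000 base is the planning rate for TB, whereas this endpoint is wider. If genuine possible cases add 50% with the same RR (assumption): (45.56 + 27) / (91.13 + 27) = 0.61.
- *Longer follow-up.* This objective covers 24–40 months, while scheduled films stop at month 24. With 18 months of even accrual (assumption), mean follow-up is 24 + 9 = 33 months. Control events are 1350 × 0.0225 × 2.75 = 83.53 and intervention 41.77: (41.77 + 27) / (83.53 + 27) = 0.62.
- *Both together:* (62.65 + 27) / (125.30 + 27) = 0.59.
- *Not every shadow is sampled.* If half of a 2% prevalence is worked up, s = 1% and the base case gives 0.59.

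**The case against.** The strongest reply is that this is a journal article. The reading categories typical and possible are not defined in it, and a reading procedure or the full protocol may already require comparison with the screening film. The objectives speak of TB developing, which an unchanged film does not naturally show. This lowers certainty about what will happen in practice. It does not remove the point, because the algorithm is printed row by row and adopted as the endpoint, and as printed it makes no such comparison.

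Several stronger readings are tempting, and the document does not support them:

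- *That the primary endpoint is contaminated through the upgrade from possible to probable.* Footnote 2 requires a clear-cut response to treatment. A symptom-free person with an unchanged scar has no symptoms to improve and no lesion that resolves.
- *That every baseline shadow becomes an event.* Each relevant row also needs a negative sputum smear, and Table 3 takes sputum only if indicated. Symptom-free people may often not be sampled, although the symptom-negative rows show that such work-up is foreseen.
- *That the entry and endpoint rules contradict each other.* One is a clinician's decision about treatment; the other is a grade of diagnostic certainty. Footnote 2 expects only some possible cases to be treated.

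It is also fair that this is a deliberately sensitive secondary endpoint beside a stricter primary, that secondary results are to be read with caution, and that bias towards 1 cannot create false efficacy. This limits the stakes but does not make the bias harmless.

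**Conclusion.** The point holds for two secondary endpoints: possible, probable or definite TB, and its composite with death. As printed, Table 1 allows a stable pre-randomisation shadow in a symptom-free, sputum-negative participant to count as an incident event. The direction, towards 1, follows from randomisation and from the fact that 3HP cannot prevent a finding already present.

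The size is unknown. An RR of 0.59 to 0.76 in place of 0.50, for counted shadows in 1% to 5% of participants, rests on an assumed prevalence, on every shadow in that range being worked up and counted, on the 45/1000 planning rate and on 2 years of follow-up. Longer follow-up, genuine possible cases or incomplete sampling all reduce it. In the composite, deaths not counted as TB reduce or increase the dilution depending on whether 3HP affects them; this was not modelled. The primary analysis and the sample size stand. The change is worth making, but the trial's main conclusion does not depend on it.

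**What to change.** For endpoint classification during follow-up, add a note to the two symptom-negative rows of Table 1 that give Possible TB on a negative smear without a positive culture or Xpert (typical film, and possible film). The x-ray counts towards Possible TB only if the abnormality is new or has progressed against the participant's own screening film, with both films read blind to arm. The note should say that it governs endpoint classification only.

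Leave every other row as it is. A blanket rule that an unchanged film means no TB would override histopathology-positive cases that Table 1 calls Probable TB, and so alter the primary endpoint. It would also reclassify newly symptomatic participants with a persistent abnormal film.

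Add one sensitivity analysis of both secondary endpoints in which possible cases with a film unchanged from screening are not counted as events. This also shows how much the untouched symptomatic rows contribute.

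Cost: a table note, a line in the reading instructions and paired reading of films that are already scheduled. A few slow-changing true cases may be missed.

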### Participant timeline {13}

Participants will be followed up in the study for at least 24 months (Fig. 1). Patients will be followed up weekly for the first 12 weeks, then monthly to month 24 (Table 3). Follow-up will continue for each participant after 24 months to the end of the trial, with follow-up after 24 months embedded in routine clinical care as per the respective country guidelines. At each post-trial visit, participants will be asked about TB symptoms and other safety outcomes. Participants may undergo investigations for diagnosis of TB, and other procedures for assessing safety, at any point during follow-up if presenting with symptoms.

**Table 3 Tab3:** Trial and sub-study assessment schedule for physical visits at study sites

	Screening	Pre-randomisation	Day 0	Week 1	Week 2	Week 3	Week 4	Week 5	Week 6	Week 7	Week 8	Week 9	Week 10	Week 11	Week 12	Month 8	Month 12	Month 16	Month 20	Month 24	Clinic follow-up to end of trial
**Trial eligibility assessment and screening sub-study I: informed consent (screening cohort** ***n*** **= 6000)**	X																				
Demographics, DM and TB (family) history, BMI, blood pressure, waist-hip circumference ^a^	X																				
TST (and reading), IGRA (Quantiferon Gold Plus), HIV	X																				
TB symptoms	X	X		X	X	X	X	X	X	X	X	X	X	X	X	X	X	X	X	X	X^g^
Chest x-ray	X																X			X	
Sputum for Xpert and culture, samples for extra-pulmonary TB, if indicated^b^	X			X	X	X	X	X	X	X	X	X	X	X	X	X	X	X	X	X	X
**Informed consent (trial** ***n*** **= 3000)**		X																			
HbA1c		X															X				
Pregnancy test		X																			
Haematology		X					X				X				X						
Chemistry (eligibility and safety)^c^		X					X				X				X						
Symptoms/adverse events^d^		X		X	X	X	X	X	X	X	X	X	X	X	X	X	X	X	X	X	X^g^
Randomisation			X																		
Dispense IP			X	X	X	X	X	X	X	X	X	X	X	X							
Treatment compliance, discontinuation^e^				X	X	X	X	X	X	X	X	X	X	X	X						
Quality of life^f^		X					X				X				X						
**Cohort study (*****n*** **= 1000)**																					
Informed consent for the cohort study		X																			
TST (and reading), Quantiferon Gold Plus		X																			
HbA1c		X																			
TB symptoms		X		X	X	X	X	X	X	X	X	X	X	X	X	X	X	X	X	X	
Chest x-ray																	X			X	
Sputum for Xpert/culture for TB assessment + samples for extra-pulmonary TB if indicated^b^				X	X	X	X	X	X	X	X	X	X	X	X	X	X	X	X	X	
**Blood samples for future laboratory studies**																					
Blood for DNA/RNA/plasma in *n* = 6000 screened and upon TB diagnosis during follow-up (*n* = ~ 100–150)	X															X					
Follow-up Quantiferon Gold Plus in trial (*n* = ~ 600) participants															X						
Blood for DNA/RNA/plasma in trial (*n* = 3000) participants during follow-up															X		X				

^a^Questionnaire (age and sex, education, socioeconomic status, use of alcohol, smoking) and clinical assessment (DM history, DM management, DM complications, TB history, history of exposure to TB, TB treatment, family history of DM and TB, BMI, blood pressure, waist-hip circumference)

^b^Investigations for TB may be carried out at any time if patients present with symptoms of TB. During the screening phase, only Xpert will be used to diagnose TB; the sample will be stored for culture. Investigations for extra-pulmonary TB will be carried out if clinically indicated according to the specified SOP ‘Handling suspected extra-pulmonary TB’

^c^Total bilirubin, AST (SGOT), ALP and Cr

^d^At baseline, all signs and symptoms that occurred within 30 days before entry will be recorded

^e^Doses must be given at least 72 h apart. Adherence will be recorded each week until the completion of treatment (or discontinuation of treatment). Allowable windows are ±2 days for weekly follow-up visits during the 12 weeks of drug administration

^f^Measured using the EQ-5D-5L as part of the cost-effectiveness sub-study

^g^Telephonic follow-up assessment schedule at months 5, 7,10, 14, 18 and 22

Lipid profile (cholesterol, triglycerides, LDL, HDL)

### Sample size {14}

We expect to screen approximately 6000 individuals in order to recruit 3000 patients with DM and LTBI for the RCT. In an unpublished case-control study (excluding HIV patients) in Uganda, the prevalence of LTBI among the DM patients as well as controls was ~ 70% using Quantiferon only.

With an incidence rate of 22.5 TB cases/1000/year, we will have 90% power to detect a RR of 0.5 or less with 3000 individuals randomised (allowing for 10% loss to follow-up). Sensitivity analyses to assess the power of our study under a range of plausible parameter estimates are shown in Table 4. Incidence rates of TB were estimated from prevalence studies, assuming an average disease duration of 2 years. With respect to efficacy, no data are available in DM patients, but a Cochrane Review of 12 trials with 8578 HIV-infected participants reported TB preventive treatment (any anti-TB drug) had a lower incidence of active TB than placebo (RR 0.68, 95% CI 0.54–0.85) [32]. The benefit was greater in TST-positive individuals (RR 0.38, 95% CI 0.25–0.57) than TST-negative individuals (RR 0.89, 95% CI 0.64–1.24) [28]. Risk reduction is expected to be at least as great for DM, and to justify policy change, we envisage that at least 50% efficacy would be needed. TB incidence is expected to stay relatively constant in people with DM (as opposed to the decreasing incidence observed in TB case contacts) which means it is worthwhile to continue follow-up for all trial participants until the last randomised participant completes 24 months of follow-up, in order to maximise power.

**Table 4 Tab4:** The total number of people needed (with 1:1 randomisation) for detecting a given reduction in risk with 90% power and a significance level of 0.025 (one-sided)

	Cumulative number of cases/1000 over 2 years of follow-up		
RR	30/1000	40/1000	50/1000
0.4	2664	1982	1574
0.5	4106	3054	2424
0.6	6834	5082	4032

### Recruitment {15}

Potential adult participants over 18 years old from hospital with DM outpatient clinics will be identified (~ 6000 in total) and approached by trained clinic staff to participate in the trial. Recruitment activities will not extend to inpatients. The target sample size will be enrolled within an anticipated accrual period of 18 months. All participants with DM will be identified for the screening phase by research staff at the participating sites.

### Assignment of interventions: allocation

#### Sequence generation {16a}

Participants will be randomised 1:1 to intervention or placebo using blocked randomisation within strata (clinical sites), with random block sizes. The randomisation list will be generated and managed by a validated module in the CASTOR database.

#### Concealment mechanism {16b}

Online randomisation will be performed in CASTOR (https://www.castoredc.com). Allocation will be concealed from all involved investigators to ensure blinding to treatment, except for the trial site pharmacists. The treatment allocation for the patient can only be viewed by those with ‘randomisation viewing rights’.

#### Implementation {16c}

A study doctor/nurse will enrol participants and do the online randomisation, which will take place after informed consent has been given, baseline data are complete, and the participant is ready to receive treatment. Patient details will be checked for completeness before randomisation. The website will then provide the treatment allocation for the patient to the site pharmacist who will afterwards prepare the allocated intervention. Blinded drug packages (in fully made-up and labelled treatment packs) with matching placebo tablets will be dispensed.

